## Abstract

**Introduction:**

Exacerbations, impaired health-related quality of life (HRQoL) and reduced exercise capacity increase the risk of hospitalisations and death in chronic obstructive pulmonary disease (COPD). However, their monitoring relies on in-person assessments, potentially delaying early care. While smart sensing technologies can enable remote monitoring, their use in predicting disease worsening remains limited. The TOLIFE Clinical Study A (CSA) aims to develop an artificial intelligence (AI) model integrating clinical data with smart sensing devices data to predict exacerbation onset and changes in HRQoL, dyspnoea and exercise capacity in people with COPD.

**Methods and analyses:**

TOLIFE CSA is a longitudinal observational study that will recruit 150 clinically stable people with COPD from three clinical sites in Spain, Italy and Germany. Over 1 year, participants will attend quarterly in-person visits to collect clinical data, while being continuously monitored using six unobtrusive smart sensing devices collecting daily metrics calculated from triaxial acceleration, angular velocity, photoplethysmogram, sound intensity, changes in latitude and longitude, ambient light intensity, biomechanical pressure and respiratory airflow parameters. Clinical outcomes are exacerbation onset through medical records; 3-month changes in HRQoL through the COPD Assessment Test and the Clinical COPD Questionnaire; 3-month changes in dyspnoea severity through the modified Medical Research Council Dyspnoea Scale; and 6-month changes in functional exercise capacity through the 6-minute walk test. We will train, internally validate and test AI-based models (Random Forests, XGBoost, multilayer perceptrons, cumulative link model and standard classification model) to predict clinical outcomes.

**Ethics and dissemination:**

Ethical approval was issued for all sites by the Ethical Commission (EC) of the Medical Association of Schleswig-Holstein (Bad Segeberg; vote 074/23 ff), EC of the Tuscany Region–North West Area (Pisa; vote CET10/2023) and EC of Parc de Salut Mar (Barcelona; vote 2023/11230). All participants will sign a written informed consent.

**Trial registration number:**

NCT06172712.

WHAT IS ALREADY KNOWN ON THIS TOPICOne barrier to early intervention in chronic obstructive pulmonary disease (COPD) is the reliance on interspersed in-person assessments to monitor key health outcomes. While smart sensing technologies are increasingly used for remote monitoring, their potential to support early intervention remains largely unexplored.WHAT THIS STUDY ADDSThis study aims to train, internally validate and test models to predict the onset of exacerbations and changes in health-related quality of life (HRQoL), dyspnoea severity and exercise capacity, with the goal of early intervention and attenuation of COPD progression.HOW THIS STUDY MIGHT AFFECT RESEARCH, PRACTICE OR POLICYThe findings will provide the development of a prediction tool that guides physicians in providing early, targeted care based on individual prediction estimates. It also fills a gap in the scientific evidence on prediction models for exacerbation onset and changes in HRQoL, dyspnoea severity and exercise capacity.

## Introduction

 Reducing symptoms, improving exercise capacity and preventing exacerbations are key treatment goals in chronic obstructive pulmonary disease (COPD).^1^ Exacerbations are particularly significant as they worsen health-related quality of life (HRQoL), reduce exercise capacity and increase the risk of future exacerbations, hospitalisations and death.^2^,^5^ Current guidelines recommend at least one annual visit for moderate-to-severe COPD and two for very severe cases to monitor disease progression, ideally including assessment of symptoms and exercise capacity.^6^ However, relevant changes in dyspnoea, HRQoL, exercise capacity or other clinical outcomes may occur between visits and remain undetected. Unfortunately, no tools are currently available for continuous monitoring of these key COPD health outcomes that would allow early identification of disease worsening and subsequent care.

Remote patient monitoring is a promising strategy for proactive COPD care, where sensor-based technologies are central to continuous data collection,^7^ and artificial intelligence (AI) is key to its subsequent integration and analysis. Sensor-based technologies, either worn on the body or placed in the home environment, continuously collect a wide range of physiological and behavioural data to support remote health assessment and potentially enable early detection of clinical deterioration.^8^ The advantages are amplified given that in respiratory disease, passive monitoring strategies (eg, wearable oxygen saturation device) achieve superior patient adherence compared with active methods (eg, manual pulse oximeter recording).^9^ Moreover, AI methods have shown potential to outperform traditional approaches in predicting COPD-related outcomes, particularly when integrating multiple data sources. For example, a random forest classifier outperformed a rule-based symptom detection method in predicting exacerbations within 3 days (area under the receiver operating characteristic curve (AUROC) 0.727 compared with 0.655),^10^ and gradient boosting models have outperformed exacerbation history alone in predicting severe exacerbations (AUROC 0.82 compared with 0.68).^11^ Moreover, combining clinical, environmental and lifestyle data improved 7-day exacerbation prediction (AUROC 0.935 compared with 0.835 when clinical data were excluded).^12^ However, there is still limited evidence on whether sensor-derived data can effectively predict key COPD outcomes or whether constructs increasingly associated with COPD progression, such as gait patterns^13^ and sleep quality,^14^ can effectively improve these predictions.

The TOLIFE Clinical Study A (CSA) aims to train, internally validate and test a modular AI-based analytical framework that integrates clinical data from standardised tests with continuously gathered daily-life data from six unobtrusive devices (smartphone, smartwatch, portable spirometer, smartshoes, smart mattress cover and environmental box). The primary prediction target is the timing of onset of moderate-to-severe exacerbations. Separate patient-specific models will address changes in HRQoL, dyspnoea severity and functional exercise capacity.

## Methods and analysis

We follow the Strengthening the Reporting of Observational Studies in Epidemiology (STROBE) guidelines within this manuscript.^15^ The study protocol represents version 2, June 2024.

### Study design

TOLIFE CSA is a longitudinal observational study that will run from May 2024 to April 2026. It includes a baseline visit (visit T1), followed by four follow-up visits every 3 months (visits T2, T3, T4 and T5, respectively) and continuous monitoring using smart sensing devices over 12 months (figure 1). All visits will take place in person at each participating clinical site.

**Figure 1 F1:**
[figure not shown]
Overview of study design and data collection schedule in the TOLIFE CSA study. 6MWT, 6-minute walk test; BIA, bioelectrical impedance analysis; CSA, Clinical Study A; DLCO, diffusing capacity for carbon monoxide; M0–M12, month 0–month 12; T1–T5, visit 1–visit 5.

### Participants

We will recruit people with stable COPD from three tertiary hospitals: Azienda Ospedaliero Universitaria Pisana (Pisa, Italy), Hospital del Mar (Barcelona, Spain) and the Pulmonary Research Institute (Großhansdorf, Germany). COPD will be defined according to the American Thoracic Society (ATS) and European Respiratory Society (ERS) guidelines as a postbronchodilator forced expiratory volume one second (FEV_₁_) to forced vital capacity (FVC) ratio of less than 0.70.^16^ Inclusion criteria are: (1) individuals with moderate-to-severe COPD (FEV_₁_ <80% of predicted) and a documented history of at least one moderate or one severe exacerbation (see definitions below) in the 12 months before enrolment; (2) age 40 years or older; (3) ability to walk at least 4 m independently, with or without walking aids; (4) availability for repeated study visits over 12 months; (5) willingness to use smart sensing devices; and (6) ability to read and write in the primary language(s) of the study site. Exclusion criteria are: (1) a history of myocardial infarction, hospitalisation for unstable angina, stroke, coronary artery bypass graft, percutaneous coronary intervention or implantation of a cardiac resynchronisation therapy device within 3 months before providing informed consent; (2) uncontrolled congestive heart disease (New York Heart Association class >3); (3) primary respiratory diseases other than COPD; (4) a history of major lung surgery (eg, lung transplant); (5) a major respiratory infection or exacerbation within 4 weeks before study inclusion or lung volume reduction within 6 months before study inclusion; (6) active treatment for cancer or other malignant diseases that could impact quality of life and adherence to the study; (7) a mental disorder that impedes effective participation; (8) a severe disease limiting survival to 1 year; (9) severe cognitive impairment (Mini-Mental State Examination <18); (10) significant mobility limitations unrelated to COPD; and (11) inability to follow study procedures due to language barriers or psychological disorders.

The target sample size was determined based on the feasibility of recruiting eligible participants within the funded study timeframe. We aim to recruit 150 participants, each contributing an average of 360 daily measurements, for an expected total of approximately 54 000 daily observations. For the primary outcome, onset of moderate-to-severe exacerbations, we anticipate at least 106 events, based on data from a large cohort study showing that individuals with a history of one moderate exacerbation experience an average of 0.71 subsequent exacerbations after a year of follow-up.^17^ According to the events-per-variable rule of thumb, predictive models should ideally include no more than one candidate predictor per 10 outcome events to reduce the risk of overfitting. With our sample size, there is a risk of prediction uncertainty and instability because we might have too many predictor variables relative to the anticipated number of outcome events. To mitigate this risk, we will perform a variable selection process to identify and retain only the most significant risk factors before developing the final predictive models. However, in our context, where the purpose is to provide early standard care, even models with moderate instability can still be useful for guiding timely decisions.^18^

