### Study status

Assessors’ training began in January 2024, totalling approximately 24 hours. Following ethical approval at all participating sites, participant recruitment was conducted from May 2024 to October 2025. As of October 2025, ninety-six participants have been recruited into the study. However, recruitment at Azienda Ospedaliero Universitaria Pisana has been delayed due to pending safety regulatory requirements for research prototype devices.

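### The expected 106 events and 54 000 daily observations assume 150 participants followed for about a year, which the reported recruitment of 96 and the April 2026 close do not deliver

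*Protocol article*

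**What the plan says.** Three current sections of the protocol article bear on this.

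- **Participants (sample size).** "We aim to recruit 150 participants, each contributing an average of 360 daily measurements", "for an expected total of approximately 54 000 daily observations". For moderate-to-severe exacerbations, "we anticipate at least 106 events, based on data from a large cohort study" in which "individuals with a history of one moderate exacerbation experience an average of 0.71 subsequent exacerbations after a year of follow-up". The paragraph then cites a guide of one candidate predictor per 10 events and concedes that there may be too many predictors for the events anticipated.
- **Study status.** "participant recruitment was conducted from May 2024 to October 2025", and "As of October 2025, ninety-six participants have been recruited into the study". Recruitment at the Pisa site is described as delayed. No extension or catch-up recruitment is stated.
- **Study design.** The study is a "longitudinal observational study that will run from May 2024 to April 2026". Each participant has a baseline visit (T1), four further visits at 3-month intervals (T2 to T5) and 12 months of device monitoring.

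No section revises the event or daily-observation totals in the light of the recruitment status, or says what happens to participants who have not reached T5 at the close.

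**The concern.** The planning totals need two things: 150 people, and about a year of observation from each. The article's own status report and calendar supply neither. With recruitment running to October 2025 and the study closing six months later, the last enrolees can reach the 6-month visit (T3) at best. Anyone enrolled after about April 2025 cannot reach T5.

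The article uses the event total to discuss overfitting and to judge the risk of instability acceptable. If that total is too high by a third or more, the discussion rests on more information than the study will have. Validation adds to the problem: training and test sets are separated by centre, so each training set holds only part of an already smaller total, and one of the three centres is delayed. The secondary models lose data as well. The 6-minute walk test is done at T1, T3 and T5, so a participant cut off before T5 loses the T3 to T5 change, which is half of that person's 6-month changes.

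**Working it through.** **Inputs from the article.** Target N = 150; recruited N = 96; rate 0.71 events per person-year; 360 daily measurements per person; recruitment May 2024 to October 2025 (18 months); study May 2024 to April 2026 (24 months); follow-up 12 months; guide of 10 events per candidate predictor.

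**Assumptions, because the article gives no figure.** Accrual is uniform over the 18 months, with linearly front-loaded and linearly back-loaded accrual as the range. There is no dropout. Observation stops at the end of April 2026.

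**Step 1: reproduce the stated figures.**
- Events: 150 × 0.71 = 106.5, stated as 106.
- Days: 150 × 360 = 54 000.

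Both agree, and both use full recruitment and a full year.

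**Step 2: 96 participants, a full year each.**
- Events: 96 × 0.71 = 68.2, which is 1 − 68.2/106 = 36% fewer.
- Days: 96 × 360 = 34 560, also 36% fewer.

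This step needs no accrual assumption.

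**Step 3: add the April 2026 close.** A person enrolled at month t (0 to 18) is followed for min(12, 24 − t) months. Under uniform accrual:
- Two thirds enrol by month 12 and have 12 months. One third enrol later and have between 12 and 6 months, 9 on average.
- Mean follow-up = (2/3 × 12) + (1/3 × 9) = 11.0 months.
- Person-years = 96 × 11/12 = 88.
- Events = 88 × 0.71 = 62.5. Days = 96 × 360 × 11/12 = 31 680.
- One third of 96, that is 32 people, would not reach T5.

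**Step 4: vary the accrual shape.** Events = N × 0.71 × mean follow-up/12; days = N × 360 × mean follow-up/12. The last column compares events with 106.

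| Scenario | Mean follow-up (months) | Share under 12 months | Events | Days | Events below 106 |
|---|---|---|---|---|---|
| 96, full year | 12.0 | 0% | 68.2 | 34 560 | 36% |
| 96, front-loaded | 11.8 | 11% | 66.9 | 33 920 | 37% |
| 96, uniform | 11.0 | 33% | 62.5 | 31 680 | 41% |
| 96, back-loaded | 10.2 | 56% | 58.1 | 29 440 | 45% |
| 150, uniform | 11.0 | 33% | 97.6 | 49 500 | 8% |

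The last row shows that the calendar alone brings the total below 106, even with the target met.

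**Step 5: the rate that would rescue 106.**
- 96 people, full year: 106/96 = 1.10 per year.
- 96 people, 88 person-years: 106/88 = 1.20 per year.

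**Step 6: the article's predictor guide.** 106/10 = 10.6; 68/10 = 6.8; 62/10 = 6.2; 58/10 = 5.8. The guide points to about 6 candidate predictors, against about 10 at the stated total.

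**The case against.** The strongest reply is that 150 is a target in a protocol version dated June 2024, while 96 is a status figure from October 2025. A target and a lower achieved count can both be true, and the article discloses the shortfall and its cause. That stands: nothing was miscalculated and nothing is hidden. It does not explain why the totals carry no update beside that status, or how 12 months of follow-up fits between October 2025 and April 2026.

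A second reply is that a delayed site may still recruit, so 96 may not be final. The article dates the recruitment period to October 2025, but the word leaves some doubt. The doubt does not restore the figure. If 54 more people joined in November 2025 with 6 months each, they would add 54 × 0.71 × 0.5 = 19.2 events. The total would then be 62.5 + 19.2 = about 82 with uniform accrual of the 96, or 68.2 + 19.2 = about 87 if all 96 completed a year.

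A third reply is that 0.71 is low for this population. It belongs to people with one prior moderate exacerbation, whereas entry also admits those with more, or with a severe one. This stands too, and it gives the wording of a minimum some basis. A reader might infer that the wording is wrong because a Poisson count with mean 106.5 would often fall below 106. That inference treats 0.71 as the exact rate, which the article does not claim. Still, 106 events from 96 people would need 1.1 to 1.2 per year, and the article offers no support for such a rate.

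A reader might also infer that an average of 360 days contradicts optional device use. The documents do not show this. The smartphone is mandatory, several devices feed the indicators, and the limitations section plans for gaps. Skipping one device need not lose a participant-day, so 360 is at most optimistic.

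Finally, the sample size was set by feasibility, and the article already admits possible instability and plans variable selection. That limits the consequence, but the admission is framed around 106 events.

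**Conclusion.** The point holds. The sample size paragraph, the recruitment status and the study calendar cannot all describe the same study. Headcount alone puts expected events and days 36% below the stated totals: about 68 events and 34 560 days. With the April 2026 close and uniform accrual without dropout, the shortfall is 41%: about 62 events and 31 680 days. Across the accrual shapes tried it is 37% to 45% (about 58 to 67 events). Any dropout would lower these figures, and a rate above 0.71 would raise them.

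Three stronger readings are not supported. The 106 is not an arithmetic error; it follows from its inputs. A shortfall of about 40% is not a fact of the article, because only the 36% is free of assumptions about enrolment dates. Nor is six predictors a binding ceiling: the article presents 10 events per predictor as a rule of thumb and fixes no number of predictors.

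**What to change.** Reconcile the Participants, Study status and Study design sections.

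1. Keep 150 as the recruitment target. Beside the status report, add an updated projection: about 58 to 68 events at 0.71 per year, with the matching daily observations (29 440 to 34 560 before any dropout or non-use), and state the accrual, dropout and close-date assumptions. The actual enrolment dates, which the sponsor holds, would replace the assumed accrual. If a higher rate is thought more suitable for this population, give it with its source.
2. Note that the article's own guide then points to about 6 rather than about 10 candidate predictors, and relate the planned variable selection to that number.
3. Resolve the calendar. Either state a close date that lets the last enrolee reach T5, or state that late enrolees are administratively censored at the close. In the second case, count their actual exposure and report how many T3 to T5 walk-distance changes, and other later visit outcomes, are lost.
4. If recruitment at the delayed site is to continue, say so and give its end date.

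The projection and the censoring statement cost a recalculated paragraph and some wording, and make the stated figures less favourable. No extra recruitment is needed. A later close would prolong follow-up, at a cost that the article does not give.

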### Statistical analysis

The characteristics of the participants will be summarised using means and SD for continuous variables and frequencies and percentages for categorical variables.

The collected data will be processed through a modular modelling architecture. Low-level models will convert raw sensor outputs from each device (continuous physiological signals, discrete events and questionnaire-derived outcomes) into standardised physiological and behavioural indicators. These indicators, integrated with clinical variables, will serve as inputs to the higher level predictive models.

To predict the onset of moderate-to-severe COPD exacerbations, both rule-based and machine learning approaches will be compared during development, with the single best performing strategy in terms of predictive accuracy and clinical interpretability selected for the final system. The model will output a continuous daily probability score estimating exacerbation risk within a given future time window, rather than a binary prediction. To predict changes in 6MWD, CAT, CCQ and mMRC outcomes, we will model their levels and their changes over time, both as continuous and dichotomised according to minimal importance difference (following the most recent literature cut-offs at the time of data analysis), using a cumulative link model or a standard classification model, respectively. Predictors will consist of sensor-derived indicators, aggregated over different temporal windows (eg, 7, 14, 21 and 30 days for the exacerbation models; 21-day summaries for the 6MWD, CAT, CCQ and mMRC models), together with clinical variables.

For all models, statistical inference will rely on a clustered bootstrap approach with resampling at the participant level to account for repeated measurements; a group-based validation strategy will be adopted, with training and testing sets separated at the clinical centre level to prevent information leakage and assess cross-site generalisability; and performance will be evaluated at both the cohort and patient-specific levels, assessing whether the models reliably detect meaningful deviations relative to each participant’s baseline over time. Standard classification metrics will be reported for all models using the Ranked Probability Score when applicable. For the 6MWD, CAT, CCQ and mMRC models, a leave-one-subject-out validation strategy will additionally be used with principal component analysis to address collinearity among predictors.

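### Keeping only the strongest predictors does not meet the plan's own limit on candidate predictors, and the text does not place that selection inside the validation

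*Protocol article*

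**What the plan says.** The sample-size paragraph of the protocol article (Participants) says that "we anticipate at least 106 events". This rests on a cohort in which people with one prior moderate exacerbation "experience an average of 0.71 subsequent exacerbations after a year of follow-up". The paragraph then gives its rule of thumb, "predictive models should ideally include no more than one candidate predictor per 10 outcome events", and admits that "we might have too many predictor variables relative to the anticipated number of outcome events". The remedy it offers on the predictor side is this: "we will perform a variable selection process to identify and retain only the most significant risk factors before developing the final predictive models". It does not name the selection method or the data on which selection is run.

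The Statistical analysis section describes sensor indicators summarised over several time windows (four are given as examples for the exacerbation models), a bootstrap that resamples participants, and "training and testing sets separated at the clinical centre level to prevent information leakage". Variable selection is not mentioned there. The Study status section reports 96 participants recruited as of October 2025, against a target of 150.

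**The concern.** There are two separate issues.

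The first is internal to the sample-size paragraph. A rule stated per candidate predictor is answered with a step that reduces the number of retained predictors. If the retained ones are picked because they relate to the outcome in the same data, the search over the full list has already spent the information that the rule is meant to protect. The final model looks small, but its overfitting reflects the whole list.

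The second is where selection sits. The only position given is ahead of building the final models, and the validation paragraph does not take it up. Splitting by centre protects against optimism only if the held-out centre's outcomes played no part in choosing the predictors. What is at stake is the credibility of the reported discrimination for the primary target, exacerbation onset.

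**Working it through.** **Inputs.** Participants section: 150 participants, 0.71 exacerbations per participant-year, 106 events, one candidate per 10 events. Study status: 96 participants. Statistical analysis: four example windows. Table 1 and Clinical data: sensors and clinical variables.

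**The plan's own figure.** 150 × 0.71 = 106.5, which reproduces the stated 106.

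**Candidates allowed (events ÷ 10).**
- 150 participants: 106 ÷ 10 = 10.6, about 10.
- 96 participants: 96 × 0.71 = 68.2 events; 68.2 ÷ 10 = 6.8, so 6 to 7.

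**Candidates implied.** The article gives no count, so this is an assumption. Table 1 has 4 + 3 + 2 + 3 + 2 + 2 + 1 + 1 + 1 + 1 = 20 device-sensor pairs. One indicator each over four windows makes 80. The Clinical data section adds about 31 variables, giving about 111. Counting one indicator per sensor row instead gives 10 × 4 = 40, plus about 33 clinical variables on a slightly different count, or 73. The range examined is 20 to 200.

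**Events per candidate.** 106 ÷ 20 = 5.3; 106 ÷ 111 = 0.95; 106 ÷ 200 = 0.53. Keeping 10 of 111 gives 106 ÷ 10 = 10.6 events per retained predictor, but still 0.95 per candidate. If all 111 were independent noise, 111 × 0.05 = 5.6 would be expected to pass p < 0.05, and the chance of at least one is 1 − 0.95^111 = 0.997.

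**Noise-only simulation.** No predictor carries any information, so the true AUROC is 0.50. Assumptions: 150 participants, three equal centres, independent predictors, 10 kept by univariate score test, logistic model, each centre held out in turn. Two data layouts were used: one row per participant (400 replicates), and weekly rows with participant-level frailty and predictor intraclass correlation 0.5 (40 replicates). Each cell shows participant rows / weekly rows.

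| Candidates | Same-data AUROC | Held-out AUROC, selection on all centres first | Held-out AUROC, selection inside training centres |
|---|---|---|---|
| 20 | 0.69 / 0.63 | 0.58 / 0.55 | 0.50 / 0.49 |
| 50 | 0.75 / 0.67 | 0.66 / 0.61 | 0.50 / 0.50 |
| 111 | 0.79 / 0.69 | 0.72 / 0.65 | 0.51 / 0.49 |
| 200 | 0.81 / 0.71 | 0.74 / 0.67 | 0.50 / 0.50 |

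The second column bears on the first issue. The number retained is always 10, yet the spurious fit grows with the number examined. The third and fourth columns bear on the second issue.

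With 96 participants, 111 candidates, 7 kept and two equal centres assumed, selection on all centres first gives 0.74 / 0.66. Selection inside the training centres gives 0.50 / 0.49.

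**Correlated predictors.** Windows of the same indicator overlap, so independence is too harsh. All runs here are noise-only with selection on all centres:
- Windows correlated at 0.8 to 0.9, 150 participants, 10 kept: 0.65 with 73 candidates and 0.66 to 0.67 with 111. With 96 participants and 6 kept: 0.67 to 0.70.
- Windows correlated at 0.85 to 0.9 and clinical blocks at 0.5 to 0.7, 73 candidates: 0.60 to 0.62 with 150 participants and 0.64 to 0.66 with 96.

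Selection inside the training centres stayed at 0.49 to 0.51.

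**The case against.** The strongest reply concerns leakage. The article never says that selection uses all centres. Selecting before fitting describes selection inside each training set equally well, and the Statistical analysis section states that preventing leakage is the purpose of the centre split. A condensed article may also leave fold-level detail, including whether the bootstrap repeats selection, to the full protocol or analysis plan. This stands. A reader might infer that the plan does leak outcomes into the held-out centres, or that its bootstrap intervals omit selection uncertainty. The text supports neither as a statement of fact.

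A reader might also take the word significant to mean p-value screening. No test or threshold is named, and selection by importance or regularisation is possible. This stands too, but any selection driven by the outcome leaves the candidate count where it was. Only outcome-blind reduction, such as clinical choice, would lower it, and the article does not say that this is meant.

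Finally, the article discloses the instability risk, calls its rule an ideal, and claims to mitigate rather than to cure. The disclosure is fair, and the limitations section adds that the tool will favour sensitivity. That deals with the clinical consequences of instability. It does not make the stated remedy act on the quantity that the rule limits.

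**Conclusion.** The stated mitigation does not satisfy the rule that it is set against. This holds on the article's own wording and needs no assumption about folds. Even the low assumed count of 20 candidates gives 5.3 events per candidate against the 10 required, and 200 gives 0.5.

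The second part is conditional. If selection were run once on all centres, the centre split would not prevent optimism. Noise alone would show a held-out AUROC of about 0.55 to 0.58 with 20 candidates and about 0.60 to 0.74 with 50 to 200, depending on predictor correlation, data layout and sample size. With selection inside the training centres it would be about 0.50. The candidate counts, equal centres, numbers retained and logistic model are assumptions.

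It is tempting to say that noise would match the AUROC of 0.727 that the Introduction cites for a published random forest. That level is reached or approached only with many independent candidates and one row per participant. Weekly rows or correlated predictors bring it down, so the comparison should not be made without those conditions.

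**What to change.** 1. Reduce the candidate list without using outcomes, by subject-matter choice and fewer aggregation windows per indicator, towards the number that the events allow. State the resulting count.
2. State that any outcome-dependent selection, window choice or tuning uses the training centres (or training subjects) only, and is repeated in every fold and every bootstrap resample.
3. Delete or reword the claim that selection mitigates too few events per candidate. Penalised fitting is an option to name in its place.

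No data collection changes. The cost is wording, more computing time, and reported performance that will look less favourable than it would with selection done once on all the data.
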